**Methods/design:**

This randomised controlled trial will recruit nicotine dependent smokers aged between 18 and 60 using social media and advertisements in Victoria, Australia. The sample target was 150 to account for drop out and non-adherence. Once informed consent has been obtained, participants complete a range of baseline measures during a face to face interview. Participants are randomly allocated to one of two online training conditions: an intervention training group (INST), which requires participants to exercise response inhibition towards smoking-related stimuli; or an active control group, which requires participants to exercise response inhibition towards household items and does not include any smoking-related stimuli. They complete the first training session during the interview to ensure the training protocol is clear. Both groups are instructed to complete a further 13 training sessions (1 per day) at home on their computer and follow-up phone calls will be conducted at three time points: post-intervention, one-month and three months. The primary outcomes are: a) rates of smoking cessation and; b) reduction in the quantity of average daily smoking at post-intervention, one and three months follow-up.

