### Primary hypotheses

Smokers who received smoking-related response inhibition training (INST program) would report significantly higher cessation rates compared to those in the active control condition at the end of the intervention, 1 month and 3 months post-intervention.Smokers who received smoking-related response inhibition training (INST program) would report significantly less cigarette consumption compared to smokers in the active control condition at the end of the intervention, 1 month and 3 months post-intervention.

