The primary and secondary hypotheses will be analysed using separate mixed-design ANOVAs and a Chi-square analysis for the binary outcome. Depending on the rate of smoking abstinence at follow up the outcome variable will be calculated as either binary (smoking abstinence: yes/no) or percent days abstinence if Chi-square analysis is contraindicated due to low numbers in each cell. For all other mixed design ANOVAs group (i.e., intervention or control) will be included as the between-subjects factor and time (survey time points) is the within-subjects factor. For the smoking reduction primary hypothesis, the repeated-measures factor will be the average number of cigarettes smoked per day at each timepoint (i.e., baseline, post-intervention, 1 month and 3 months post intervention). For the secondary hypotheses, the repeated-measures factor will be craving or nicotine dependence at each timepoint. The predictor hypotheses will be examined using separate moderated regression analyses, with group as the predictor variable, impulsivity and dose as the moderator variable and change in smoking as the dependent variable.

The two mediation hypotheses will be analysed utilising a linear mixed model approach to examine whether the effects of INST training on level of smoking will be mediated by devaluation of smoking stimuli or an independent measure of response inhibition (SSRT).

The exploratory questions related to self-confidence and motivation will be examined using a separate mixed-design ANOVA, with group included as the between subjects factor and self-confidence and motivation at each timepoint included as the repeated-measures factor.

Repeated measures ANOVAs will be performed on “go” reaction times and “no-go” accuracy to examine stimulus-specific learning effects (100% stimuli vs. 50% stimuli) over time (first vs. fourth training session as per the analysis by Lawrence and colleagues to allow comparability). Evidence of learning across the two time points will be indicated by faster reaction time on 100% go stimuli and fewer errors on 100% no-go stimuli. Any further exploratory analyses will be labelled as such in the publication.

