#### Power analysis

As previous ICT studies have not targeted abstinence the current study was powered on smoking reduction based on Lawrence et al., [36] weight reduction ICT outcome data. Power analysis conducted via G*power indicated that an overall sample size of 92 is required to detect a medium effect size (approximately .50 cohen’s d based on Lawrence et al.) at the .05 alpha level using linear techniques (power = .80). Given that it is expected that approximately 25% will be lost to follow-up and up to 30% would not complete a minimum of 4 sessions, the target of the current study was set at 150 at the time of trial registration. However, estimated target sample may be amended if attrition is better than expected.

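### The cessation outcome is replaced by percent days abstinent if quit counts are low, so the observed data decide which variable is primary; another test of the same yes/no outcome would avoid this.

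*Protocol article*

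**What the plan says.** The Abstract (Methods/design) names two primary outcomes: "The primary outcomes are: a) rates of smoking cessation and; b) reduction in the quantity of average daily smoking". Under Primary hypotheses, the first is that the intervention group "would report significantly higher cessation rates compared to those in the active control condition", at the end of the intervention and at 1 and 3 months.

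The Analysis plan assigns "separate mixed-design ANOVAs and a Chi-square analysis for the binary outcome". The next sentence makes the form of the cessation outcome conditional on the data: "Depending on the rate of smoking abstinence at follow up the outcome variable will be calculated as either binary (smoking abstinence: yes/no"), or else "percent days abstinence if Chi-square analysis is contraindicated due to low numbers in each cell".

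The rule gives no number for a low count. It does not say whether observed or expected counts are meant, or whether one time point or all three decide. The article names no exact or other small-count method for the binary outcome. The Power analysis is built on smoking reduction and gives no expected quit rate for either arm.

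**The concern.** The chi-square test relies on a large-sample approximation that is unreliable when expected counts are small. That is a property of the test. Whether a participant has stopped smoking is equally well defined with 3 quitters or 30, so the natural response to sparse data is a different test of the same outcome. The plan instead changes the question.

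Percent days abstinent is a different quantity from the cessation rate. A participant who skips a few days and goes on smoking raises it without quitting. After a switch, the reported primary analysis would therefore not test the first primary hypothesis. Because the trigger is undefined, two analysts following the text faithfully could report different primary outcomes from the same data.

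**Working it through.** **Is there a figure in the plan to reproduce?** Not for cessation. The only sample-size result, "an overall sample size of 92 is required to detect a medium effect size", concerns smoking reduction, and nothing below depends on it.

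**Inputs from the article**
- Recruitment target 150 (Power analysis). Balanced blocks of ten (Randomisation) imply 75 per arm.
- About 25% expected loss (Power analysis): 75 × 0.75 = 56.25, so about 56 per arm with data.

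**Assumptions, not in the article**
- Quit rates between 2% and 20%, shown as control v intervention.
- A threshold of 5, applied in two ways because the text fixes neither: (E) an expected count below 5; (O) an observed cell below 5.

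**Step 1: what each trigger means.** With equal arms and T quitters in total, the expected number of quitters per arm is T/2. Trigger E therefore fires when T < 10, that is, below 10/150 = 6.7% overall at 75 per arm, or 10/112 = 8.9% at 56 per arm. It depends only on the pooled total. With quitter counts x and y in the two arms, trigger O fires, at the quit rates considered, when min(x, y) < 5. It therefore also depends on how the quitters divide between the arms.

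**Step 2: chance of switching.** With X ~ Bin(n, p₁) and Y ~ Bin(n, p₂) independent, sum P(X = x)·P(Y = y) over all tables that meet the trigger.

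| Quit rates | 75/arm, E | 75/arm, O | 56/arm, E | 56/arm, O |
|---|---|---|---|---|
| 2% v 2% | 99.9% | >99.9% | >99.9% | >99.9% |
| 5% v 5% | 78% | 90% | 95% | 98% |
| 10% v 10% | 6% | 22% | 31% | 55% |
| 5% v 10% | 30% | 72% | 67% | 90% |
| 5% v 15% | 6% | 68% | 30% | 86% |
| 5% v 20% | 0.6% | 68% | 9% | 85% |

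At 5% v 20% and 75 per arm, the choice of reading alone moves the chance of a switch from 0.6% to 68%.

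**Step 3: does the binary outcome still carry information where the switch fires?** Yes. Two-sided Fisher's exact test gives p = 0.028 for 0/75 v 6/75 (expected quitters per arm 6/2 = 3.0) and p = 0.034 for 1/75 v 8/75 (9/2 = 4.5). Both tables meet either trigger. At 5% v 20% and 75 per arm, Fisher's power is 76%, and 60 of those 76 points lie in tables that meet trigger O.

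**Step 4: what does an exact test cost?** At 75 per arm, Fisher's actual type I error at nominal two-sided 0.05 is 0.002, 0.015, 0.027 and 0.029 for common quit rates of 2%, 5%, 10% and 15%. It never exceeds 0.05 but is conservative when few quit. Power is 13% for 5% v 10%, 44% for 5% v 15% and 76% for 5% v 20%.

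**The case against.** The strongest defence is that the fallback and its condition are written down in advance, and the condition is sparse data rather than a p-value. That stands. A reader might infer that the sponsor is free to pick the primary outcome after seeing results, but the text does not support this. On the expected-count reading the switch depends only on total quitters, so type I error need not be inflated. Dependence on the difference between arms arises only on the observed-cell reading.

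It is also fair that an exact test does not rescue the cessation comparison: at 5% v 10% it would detect a difference about 13% of the time. The trial was openly powered on the other primary outcome, which this rule leaves untouched. Nor does the article say that quit counts would go unreported after a switch.

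The full plan may hold a numeric trigger and per-visit details, which articles often omit. That would settle the ambiguity but not the stated rule that the outcome itself changes. The 56-per-arm figures describe participants with data; the Analysis plan includes all participants, with multiple imputation if appropriate, so 75 per arm is the main case.

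Two stronger readings should be resisted. A reader might conclude that percent days abstinent is bound to break the ANOVA assumptions because daily smokers have almost no smoke-free days. Skewness is plausible, but the eligibility criteria exclude only smoke-free periods of two weeks or more, participants must be motivated to attempt quitting, and the Analysis plan provides for checking assumptions and addressing violations. A reader might also want participants of unknown status counted as smoking. That is a separate missing-data question and does not follow from this rule.

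**Conclusion.** The concern holds in this form: a stated rule lets observed abstinence counts decide whether the cessation outcome is quitting or percent days abstinent, without a defined trigger, and the replacement does not test the first primary hypothesis. The reason given for switching is a limitation of one test, and other tests do not share it.

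How often it would matter cannot be fixed from the article. Over the assumed quit rates the chance of a switch at 75 per arm runs from under 1% to over 99%. It is likely if about 5% or fewer quit in both arms. If single observed cells are the trigger, it stays likely even with a sizeable group difference. These figures rest on the assumed quit rates, equal arms and a threshold of 5. Whether the switch occurs does not bear on the smoking-reduction outcome.

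**What to change.** In the Analysis plan, replace the conditional sentence with a fixed one:
- Abstinence yes/no is the cessation outcome at post-intervention, 1 month and 3 months, whatever the counts.
- It is analysed by Fisher's exact test (or exact or penalised logistic regression), reported with the risk difference and its 95% confidence interval.
- Percent days abstinent is a named secondary outcome, reported in every case.

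The change takes about one sentence and needs no new data. Its price is the conservatism of Fisher's test at low quit rates. It does not raise the power for cessation, and the report should say so, so that a non-significant result is not read as evidence of no effect on quitting.

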Two meta-analyses have found that inhibitory control training resulted in an overall significant effect (albeit a small effect size), with GNG training yielding larger (medium) effect sizes than SST training [29, 33]. According to the Behaviour Stimulus Interaction (BSI) theory [38] behavioural changes induced by the GNG training are mediated by changes in evaluations of the stimuli used in the task. That is, positively regarded stimuli will become associated with negative affect as a result of consistently being paired with no-go cues. This is thought to devalue the stimuli and minimise the likelihood of approach behaviours occurring towards the stimuli in real life. This theory has been supported by evidence in studies targeting alcohol consumption that suggest a mediating effect of changes in implicit attitudes on alcohol intake [34, 39]. In the food domain, there is evidence of devaluation of trained no-go food stimuli as assessed by visual analogue scales [36, 40, 41]. Another proposed mechanism of response inhibition training is the automatic inhibition hypothesis (AIH) [32], which posits that automatic response inhibition can develop over practice if stimuli are consistently associated with stopping [42, 43]. These two potential mediating hypotheses will be investigated in this trial.

In summary, given that significant effects of the GNG task were found despite the use of non-clinical samples, it was expected that these interventions would be particularly effective with smokers as smoking receives the most frequent reinforcement compared with other dependent populations, with multiple smoking sessions each day. Furthermore, we hypothesise that it will be particularly beneficial for heavy smokers who report the greatest difficulty with impulse control [4]. This is suggested by findings that stronger nicotine dependence is associated with poorer inhibitory control [44]. Thus, this is the first study to use the GNG task in a sample of individuals who have a Tobacco Use Disorder according to DSM-5 criteria and who wish to quit/reduce smoking.

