### Predictor/moderator hypotheses

Individuals reporting high levels of impulsivity would report significantly improved outcomes from the intervention training compared to those with lower levels of impulsivity^.^Individuals who completed a greater number of sessions (i.e., dose) would report significantly improved outcomes from the intervention training compared to those who completed less sessions.

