#### Inclusion criteria

Aged between 18 and 60 years.Smoke, on average, a minimum of 10 cigarettes per day for the last 12 months.Meet criteria for moderate or above Tobacco Use Disorder defined by the DSM-5 [45].Be motivated to make a quit attempt during the training stage of the intervention.Completed at least Year 9 (or equivalent) schooling.Have computer and internet access during the intervention phase of the study.

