### Analysis plan

All participants will be included in the intent-to-treat analyses for the primary and secondary hypotheses. If relevant, per protocol analysis will include those who complete at least four sessions of the training (as per Lawrence et al. [36]) and achieve a training accuracy of at least 70%. SST data will be included for those who yield an accuracy of 40–60% on stop trials and at least 70% on go trials. Prior to analyses, all variables will be examined through IBM Statistical Package for Social Sciences (SPSS Version 25) for accuracy of data entry, missing values and fit between their distributions and the assumptions of multivariate analysis. Any violations will be addressed as per standard protocols [64].

Missing data will be managed using SPSS. First, a missing value analysis will be conducted to determine the percentage and pattern of missing data. If missing data are found to relate to a measured participant variable, those variables will be included as covariates in the analyses. If appropriate, multiple imputation will be used to replace missing values and the imputation model will include baseline covariates and outcome data. Missing data will be imputed using the Markov Chain Monte Carlo method or the Monotone method, contingent upon the pattern of missing data. A minimum of five imputed datasets will be produced [65]; however, depending on the percentage of missing data, a minimum of 20 imputed datasets may be required [66]. Wherever possible, results from the complete case analysis will be compared with results based on imputed data. If there are important differences, explanations will be offered.

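### The moderated regressions use an undefined change in smoking with no baseline cigarettes-per-day term, which costs power for the group-by-moderator tests

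*Protocol article*

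**What the plan says.** The Predictor/moderator hypotheses section of the Protocol article makes two predictions, one on impulsivity and one on number of sessions completed. The first reads: "Individuals reporting high levels of impulsivity would report significantly improved outcomes from the intervention training compared to those with lower levels of impulsivity".

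The Analysis plan says: "The predictor hypotheses will be examined using separate moderated regression analyses", and gives the variables in each as follows: "with group as the predictor variable, impulsivity and dose as the moderator variable and change in smoking as the dependent variable". It does not define change further.

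The only rule on covariates, also in the Analysis plan, is conditional on missingness: "If missing data are found to relate to a measured participant variable, those variables will be included as covariates in the analyses".

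Baseline smoking is available. Table 1 schedules TLFB at T1, and the smoking-reduction ANOVA uses the "average number of cigarettes smoked per day at each timepoint (i.e., baseline, post-intervention, 1 month and 3 months post intervention".

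**The concern.** In the moderated regressions, baseline cigarettes per day enters only inside the change score. Under the covariate rule it would be added only if it happened to predict missingness. Subtracting baseline with a fixed coefficient of 1 leaves more residual variance than estimating that coefficient. The interaction tests then have less power than the collected data allow.

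Interpretation is a second matter, for impulsivity only. Entry requires participants to "Smoke, on average, a minimum of 10 cigarettes per day for the last 12 months", with no stated upper limit, so an absolute reduction can scale with starting level. The Background says that "stronger nicotine dependence is associated with poorer inhibitory control", and expects of the training that "it will be particularly beneficial for heavy smokers who report the greatest difficulty with impulse control". If the training effect grows with baseline smoking and BIS-11 scores track baseline smoking, part of a group-by-impulsivity term could reflect smoking level.

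**Working it through.** The plan gives no figure for the moderation tests, so there is none to reproduce. The sample size of 92 in the Power analysis section concerns smoking reduction, and nothing below depends on it.

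**Inputs from the document.** Target 150; expected loss 25%, so 150 x 0.75 = 112.5, taken as 112; alpha .05 (taken as two-sided); balanced arms; design effect d about 0.50.

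**Assumptions, because the document gives no values.** Absolute change; equal SD at baseline and follow-up; rho 0.3 to 0.7; an interaction of 0.5 SD per SD of moderator; BIS-baseline correlation r from 0 to 0.5. Where a scale is needed, mean 20 and SD 8 cigarettes per day.

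**1. Residual variance (outcome SD = 1).** Change score: 2(1-rho). Baseline-adjusted: 1-rho^2. Ratio adjusted/change: (1+rho)/2.

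| rho | change | adjusted | ratio |
|---|---|---|---|
| 0.3 | 1.40 | 0.91 | 0.65 |
| 0.5 | 1.00 | 0.75 | 0.75 |
| 0.7 | 0.60 | 0.51 | 0.85 |

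**2. Power at N=112 with r=0.** With group coded -0.5/+0.5 and a standardised moderator, the interaction has variance of about (residual variance)/(0.25N) = (residual variance)/28. At rho 0.5, z = 0.5/sqrt(1.00/28) = 2.65 for change and 0.5/sqrt(0.75/28) = 3.05 for adjusted. Large-sample power is then about 75% and 86%. Simulation, which uses the t distribution and a randomly drawn moderator, is slightly lower:

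| rho | change score | with baseline |
|---|---|---|
| 0.3 | 59% | 77% |
| 0.5 | 72% | 84% |
| 0.7 | 90% | 94% |

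**3. Does omitting baseline bias the group-by-impulsivity test?** With no group-by-baseline effect it does not: simulated type I error was 4.6% to 5.4% for r of 0, 0.2 and 0.4. With a group-by-baseline slope b, the carry-over into the interaction is b x r. For b = -0.5 and r = 0.4 that is -0.20. Simulation at N=92 gave -0.201, with rejection of 15.0% for the change score, 17.7% with a baseline main effect, and 5.2% once group x baseline was added.

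**4. False-positive rate of the plan's model under a uniform percentage cut.** There is no impulsivity moderation, baseline has a minimum of 10, and rho is 0.5 or 0.7. A 20% cut corresponds to the design effect: 0.50 x 8 = 4 cigarettes, and 4/20 = 20%.

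| cut | N | r=0.3 | r=0.5 |
|---|---|---|---|
| 20% | 112 | about 6% | about 7% |
| 30% | 150 | 7-8% | 10-13% |
| 50% | 150 | 9-11% | 18-24% |

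These rates are orders of magnitude. They move with rho and with how the entry minimum is imposed on the simulated baseline. At N=150, adding baseline alone did not remove the excess at r=0.5 (12-15% for a 30% cut, 24-32% for a 50% cut). Adding group x baseline brought every setting to about 5%.

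**5. Price of group x baseline.** Its variance factor is about 1/(1-r^2): 1.10 at r=0.3 and 1.33 at r=0.5. At r=0.5 and rho 0.5 the residual term becomes 0.75 x 1.33 = 1.00. The plan's model has 2(1-rho) - r^2(1-rho)^2 = 1.00 - 0.0625 = 0.94, because BIS itself absorbs some baseline variance. At rho 0.7 the figures are 0.51 x 1.33 = 0.68 against 0.60 - 0.0225 = 0.58. Simulated power at N=112 falls accordingly, from 74% to 70% at rho 0.5 and from 92% to 87% at rho 0.7.

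**The case against.** The strongest objection is that the plan never says the change is absolute. If it is percent change, a uniform percentage cut does not vary with impulsivity and the interpretation problem goes. If it is residualised, the precision loss goes. The sentence also names only the role of each variable, and a condensed article may leave covariates of a non-primary model to the full plan. This partly stands, and the power figures are therefore conditional on absolute change. But the article does state an outcome, it leaves that outcome open to readings that answer different questions, and the one covariate rule it gives would bring in baseline only by chance.

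A reader might infer that the group-by-impulsivity test is confounded by baseline smoking. The document does not support that. Under randomisation the interaction is unbiased unless the training effect varies with baseline level. The BIS-baseline correlation is also only suggested: the Background links dependence to response inhibition, whereas BIS-11 is self-reported trait impulsivity and response inhibition is measured separately by the SST. The entry criteria may restrict the range further. Finally, the hypothesis as worded predicts that impulsive participants improve more, and in the scenarios of step 4 they do reduce by more cigarettes. Whether impulsivity acts independently of smoking level is a further question.

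A reader might also conclude that group x baseline should be mandatory. Step 5 shows why not: where the correlation is strongest, that model can have less power than the plan's own.

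**Conclusion.** The point holds as one of precision and specification in the moderated regressions. If change is absolute with equal variances, omitting baseline leaves the residual variance 1.18 times (rho 0.7) to 1.54 times (rho 0.3) what it need be, the reciprocals of 0.85 and 0.65. At N=112 and the assumed interaction this costs about 18, 12 and 4 points of power at rho 0.3, 0.5 and 0.7. The power figures were worked for impulsivity. They take the moderator to be equally distributed in both arms and unrelated to baseline, which need not hold for dose.

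Misattribution to impulsivity is a conditional caution. It needs both a training effect that scales with baseline smoking and a BIS-baseline correlation. For a 20% cut with r of 0.3 or less the error rate stays near nominal, and it becomes material only with larger cuts and r near 0.5. The argument does not extend to dose: sessions completed is a post-randomisation variable, and adjusting for baseline does not make that comparison randomised. The mixed-design ANOVAs and the Chi-square test for the primary and secondary hypotheses are not affected.

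**What to change.** In the Analysis plan:

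- Define the outcome of the moderated regressions as follow-up cigarettes per day at a named timepoint, or as absolute change. Once baseline is in the model, the two give the same interaction estimate.
- Add baseline cigarettes per day as a covariate in each moderated regression, alongside group, the centred moderator and group x moderator.
- For the impulsivity model only, report a sensitivity analysis that adds group x baseline cigarettes per day. Do not claim moderation by impulsivity independent of smoking level unless the group x BIS term is consistent there.
- If percent or residualised change was intended, say so and state the question it answers.

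The cost is a few sentences and one extra term per main model, from TLFB data already collected at T1. The sensitivity model loses precision when BIS and baseline are correlated, by the factor 1/(1-r^2) above, which is why it is placed as a sensitivity analysis. A wider interval there should not by itself be read as evidence against moderation.

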#### Randomisation

Immediately following the completion of the baseline assessment, participants began the online training task. Participants were automatically randomised to either the intervention or the control training task via a pre-computed randomisation procedure. A permuted block randomisation procedure was utilised [46] whereby participants were allocated to the intervention or control group through the use of a randomly generated number. The permuted blocks were organised in groups of ten, the details of which were not known by investigators involved with the administration of the trial. The use of the permuted block randomisation process ensures that intervention group numbers will be balanced at the end of each block and is thus the recommended process in studies with smaller samples.

Upon finishing this task participants were instructed to complete the online training task once per day for the next 13 days, totalling 14 sessions. They were asked to rate their smoking craving level before and after each training session. Twice per week, participants were sent text reminders to complete the training. All data from the online training task and outcome measures were securely stored on the Deakin University server and linked to an anonymous participant ID number such that only de-identified data were available to researchers. The data was checked for training task performance accuracy and participant adherence to the training protocol by a research assistant who was independent from investigators and not involved in data collection or analyses.

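### The missing-data covariate rule is not limited to baseline variables, and the dose and per-protocol analyses rest on behaviour after randomisation without being labelled non-randomised

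*Protocol article*

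**What the plan says.** Four statements in the protocol article bear on this.

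- **Covariates (Analysis plan).** "If missing data are found to relate to a measured participant variable, those variables will be included as covariates in the analyses". Nothing confines this to variables measured before allocation. The imputation model, by contrast, is described as holding baseline covariates and outcome data.
- **Dose (Predictor/moderator hypotheses; Analysis plan).** The hypothesis is directional: "Individuals who completed a greater number of sessions (i.e., dose) would report significantly improved outcomes from the intervention training". It is tested by regression with group as predictor and "impulsivity and dose as the moderator variable and change in smoking as the dependent variable".
- **Per-protocol set (Analysis plan).** If relevant, the "per protocol analysis will include those who complete at least four sessions of the training" and who "achieve a training accuracy of at least 70" per cent.
- **Main analysis set (Analysis plan).** "All participants will be included in the intent-to-treat analyses for the primary and secondary hypotheses".

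On timing, the Randomisation section states: "Participants were automatically randomised to either the intervention or the control training task via a pre-computed randomisation procedure". Allocation comes before the first session, so every session counted as dose is done on the allocated task.

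**The concern.** Randomisation balances what exists before allocation. Sessions completed and training accuracy come afterwards and may depend on the arm, on motivation and on smoking itself. The article gives specific reasons to expect such links:

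- Participants are asked to train preferably while craving (Inhibition training task).
- The post-intervention interview asks about smoking over the same fortnight in which sessions are counted (Post-intervention), so smoking and session count can influence each other.
- Accuracy is scored on different tasks. The intervention has fixed go and no-go mappings for smoking and relaxing images, while the control's household images are split equally (Intervention group; Control group). The Analysis plan itself expects fewer errors on always-no-go images as learning occurs, so the 70% rule may select differently by arm.

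Two things are at stake. The covariate rule could reach the primary estimate. The dose and per-protocol results could be read as evidence of efficacy or dose-response: the dose analysis tests a stated hypothesis of benefit, and only further, unplanned analyses are to be labelled exploratory.

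**Working it through.** The plan gives no figure on this point to reproduce. The calculation below shows how large the problem can be and when it disappears.

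**Inputs from the article.** Target 150 in two arms in balanced blocks of ten, so 75 per arm; up to 30% expected to complete fewer than four sessions; powered for d of about 0.50 (Randomisation; Power analysis).

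**Assumed, not in the article.** No training effect. A latent motivation score correlates 0.5 with the outcome (more motivated, less smoking). Sessions correlate with motivation r₁ in INST and r₀ in control. INST engagement is lower by δ SD. Sessions are treated as continuous and nobody is lost, for simplicity.

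**1. Sessions as a covariate in the main model.** Bias in the group effect ≈ 0.5 × mean(r₁, r₀) × δ.
- r₁ = 0.6, r₀ = 0.2, δ = 0.5: 0.5 × 0.4 × 0.5 = 0.10 SD in favour of INST, one fifth of the design effect (0.10 / 0.50).
- r₁ = r₀ = 0.4, δ = 0.5: the same 0.10 SD.
- δ = 0: zero.

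Simulations under these settings gave 0.09 to 0.10 SD. The sign follows because, at an equal session count, participants in the less engaging arm are the more motivated ones.

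**2. Group-by-dose interaction.** Spurious slope difference = 0.5 × (r₁ − r₀).
- 0.6 v 0.2: 0.5 × 0.4 = 0.20 SD per SD of sessions.
- Residual variances: 1 − (0.5 × 0.6)² = 0.91 and 1 − (0.5 × 0.2)² = 0.99.
- SE = √(0.91/75 + 0.99/75) = 0.159; z = 0.20 / 0.159 = 1.26.
- Two-sided rejection at 5% ≈ Φ(1.26 − 1.96) = Φ(−0.70) ≈ 24%. Simulations gave 22–25%.
- Equal correlations: slope difference zero, rejection about 5%.

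**3. Per-protocol contrast (session rule only).** Bias = 0.5 × (r₁λ₁ − r₀λ₀), where λ is the mean standardised engagement among those retained. If 30% of controls fail the rule, λ₀ = 0.497. With δ = 0.5, 51% of INST are retained and λ₁ = 0.782.
- r₁ = r₀ = 0.4: 0.5 × 0.4 × (0.782 − 0.497) = 0.06 SD in favour of INST.
- 0.6 v 0.2: 0.5 × (0.6 × 0.782 − 0.2 × 0.497) = 0.185 SD in favour of INST. Simulations with other session scales and cut-offs gave 0.11 to 0.17 SD.
- Equal correlations and δ = 0: zero.

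**4. Direction.** It is not fixed. In a separate simulation (N = 150) with no motivation–session link in INST but one in control, the per-protocol bias was about 0.11 to 0.12 SD against INST. False-positive rates were about 9% (per-protocol) and 26–30% (interaction).

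**5. Intent-to-treat, unadjusted for sessions.** In that same set of simulations its false-positive rate stayed at 4.7–5.8% in every scenario, including the extreme ones.

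The effect of the accuracy rule was not quantified; the article gives nothing to calibrate it.

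**The case against.** The strongest case on the other side has four parts.

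- **The main conclusions are protected.** Primary and secondary hypotheses are analysed by intent-to-treat, the per-protocol set is conditional, and dose sits under its own hypothesis heading. This stands: neither analysis touches the intent-to-treat results.
- **A variable tied to dropout may well be a baseline one.** Age or baseline nicotine dependence could qualify, and adjusting for either keeps the randomised comparison. The adjacent sentence also speaks of baseline covariates. A reader might infer that the rule necessarily puts post-randomisation variables into the primary model; the text does not say so. What remains is that it does not exclude them. The baseline wording governs the imputation model, and sessions completed is named in neither place.
- **The sizes need assumptions that the article does not supply.** The control is active and similar, image types are not disclosed beforehand, and reminders are described for all participants, all of which works against differential engagement. With equal engagement and equal correlations there is no bias, and the control arm's own dose slope removes the ordinary tendency of motivated people to train more. This stands: the bias is possible, not shown.
- **The four-session cut-off follows the food-training trial on which the task is modelled.** Comparability is a fair reason to keep the per-protocol set. It does not make the contrast randomised.

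**Conclusion.** The point holds in a limited form. The covariate rule is the more important part, because as written it can admit sessions completed into the primary model; under the assumptions shown that moves the group effect by about 0.10 SD when INST engagement is 0.5 SD lower, and by nothing when engagement is equal. The dose and per-protocol analyses condition on post-randomisation behaviour and are not labelled accordingly. Their error ranges from none to about 22–25% false positives for the 0.6 v 0.2 interaction case, and from zero to 0.06–0.185 SD for the per-protocol cases with lower INST engagement, in either direction depending on how the arms differ.

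Two stronger readings are not supported. One is that the trial's primary result is already biased: intent-to-treat is the main analysis, and a baseline covariate would do no harm. The other is that the dose and per-protocol estimates must be biased: that requires engagement, or its link to motivation, to differ by arm, and the article gives no data on either. This merits a change to the plan but does not undermine the design.

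**What to change.** - Restrict covariates in the analysis models to variables measured before randomisation.
- Put post-randomisation predictors of missingness, such as sessions completed, in the imputation model only.
- Keep the dose and per-protocol analyses, but report them as observational and supportive, and state that no efficacy or causal dose-response claim rests on them.
- Optionally, add an instrumental-variable estimate with randomised group as the instrument for INST sessions received. These are zero by design in control, who are offered INST only after data collection. State the exclusion assumption (allocation acts only through sessions) and the linearity assumption. It should not replace the dose analysis: with one binary instrument it essentially rescales the intent-to-treat effect by mean sessions received, so it cannot test whether more sessions give more benefit.

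The cost is a few sentences in the Analysis plan and no new data. The optional estimate adds one model, and its interval would be wider than that of the per-protocol contrast.
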